#### Process data

To assist in our understanding of how program characteristics may influence outcomes for a given clinic and overall, a research assistant will use a standardized tool to assess each clinic monthly for relevant stockouts and staff shortages relating to child contact management.

### Data management

A child contact management record will be implemented and maintained by healthcare workers. The child contact management record will be maintained at the health facility in both the intervention and control clinics. Additionally, in Ethiopia, health extension workers will maintain a record in the community at the health post (intervention arm only). These data will be synced with the clinic file monthly. Data will be extracted retrospectively from these routine clinic charts either onto clinical research forms (Ethiopia) or directly into a REDCap database (South Africa), no less than one month after the clinic visit to allow sufficient time for charting.

Data will be entered and maintained on a secure, password-protected, web-based REDCap database with multisite access with secure web authentication and secure sockets layer encryption. The data constitutes a limited data set and does not include identifiers like name, date of birth, address or phone number, medical record number, and identity number.

This small, unmasked study presents minimal risk to study participants and therefore does not meet criteria for a data safety and monitoring board.

### Quality management

Quality control procedures will include a review of each clinical research form for accuracy and missing values, followed by queries to assess for missing values and consistency of responses across forms. A Johns Hopkins study coordinator will monitor the performance of all procedures to ensure they are in line with the study protocol including auditing both the abstraction and data entry processes with the purpose of identifying erroneous practices and to correct any drift in performance. Five percent of all abstracted files will be compared to their source documents for accuracy.

### Responsibilities of coordination center

Johns Hopkins University will be the coordinating center responsible for ensuring each site’s IRB has approved the protocol, consent/assent forms, and any amendments and will ensure teams have the most current versions of all documents (protocol, ICFs, SOPs, etc.). They will also manage the REDCap database and quality check the data. Finally, they will be responsible for evaluating and coordinating reporting on any protocol events.

### Statistical analysis

#### Primary and secondary outcome analyses

Summary statistics of the enrolled index patients will be presented stratified by arm and study site. Analysis of the primary outcome of the number of child contacts less than of 15 years of age in Ethiopia and less than 5 years of age in South Africa who initiate TPT per index patient diagnosed will be stratified by country. Cluster-level ratios will be compared between arms using an unpaired t-test which has been shown to be robust for a relatively small number of clusters [24]. The ratio of the study arm mean ratios and the corresponding 95% confidence interval will be calculated. A log-transformation of the cluster-level ratios will be applied before applying the *t*-test if the outcomes are highly skewed. If the number of index patients varies substantially between clinics, weighted (by clinic size) mean ratios will be used. If the sample size allows, we will compare the numbers of children started on TPT between arms stratified by TPT regimen (3HP vs 3RH) and children’s age groups (^3^5 vs <5 for Ethiopia).

Secondary outcomes to be compared between arms will be the number of child contacts identified (using index patient’s clinic-based contact tracing report, the child contact management file, and the community-level file maintained by the community health team) per index patient, and the proportions of these who are screened, initiated on TPT and who complete TPT. As done for the primary outcome, cluster-level summaries for secondary outcomes will also be compared between arms. Count outcomes will be compared using Poisson regression, and cluster-level proportions (after a log-transformation, if necessary) will be compared using a *t*-test.

We will provide summary statistics of TPT completion rates and losses to follow-up discontinuation (due to incident TB, side effects, transfer out, other reasons, or death) stratified by study arm and site. TPT completion will be defined as three monthly follow-up visits over a 4-month period (3HP or 3HR) or six monthly visits over a 9-month period (6H). Loss to follow-up will be defined as no return visit within three months of the child’s last recorded visit. Other reported outcomes will include new HIV diagnoses among children who are referred for ART initiation. All outcomes will be summarized by the study arm, and formal statistical tests will be conducted if the number of events observed allows. All data will be abstracted by study staff from index patient and child contact management files.

Acceptability of the intervention will be assessed as the proportion of child contacts who are identified and whose families agrees for them to be screened by community-based clinic staff (community health worker, professional nurse, type of provider dependent on the setting) in their home. We will also summarize reasons for the refusal of a household visit in the intervention arm using proportions among those approached. Fidelity to guidelines will be summarized as the proportion of TB contacts initiated on the correct TPT regimen by age and HIV status, and the proportion of TPT initiations with the correct dose for weight to measure guideline fidelity of community-based TB preventive care.

Process outcomes to be reported will include drug shortages and stockouts, stockouts of supplies needed for pediatric specimen collection, stockouts of TB and contact file and registers, other materials needed for the intervention (scale, etc.), staffing within the TB clinic and community health teams, use of community health teams to do contact tracing in control clinics, changes in key personnel including community health workers and TB nurses, and time the TB nurse and/or community health worker is pulled away from TB activities.

All analyses will be conducted using STATA software (StataCorp. 2021) [25].

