The unblinded study statistician conducted constrained randomization balancing on baseline characteristics of the clinics that we believed would be associated with the primary outcome, including clinic geography and typical TB notifications [24]. We used STATA’s *cvcrand*function with the default balance metric which is the absolute value of the sum of the weighted differences in mean levels of covariates between the intervention and control arms [25, 26]. We assumed equal weights for all the covariates. In South Africa, the available characteristics were urban/rural stratification, sub-district and the number of TB diagnoses in the clinic averaged between 2019 and 2020 (an average was taken to account for anticipated recovery in TB notifications in 2021 after COVID-related lockdowns). Four of the clinics had much higher rates of TB diagnosis relative to the other 14 and we therefore created a size stratification so that these four clinics were placed in their own stratum. We ran *cvcrand* to generate up to 50,000 possible randomization sequences. In constrained randomization of clusters, one ought to not only consider balance on baseline covariates, but also *validity*of the set of acceptable randomization sequences from which a final one is selected [24]. The concept of validity implies that all possible pairs of clusters should be assigned to the same arm roughly 50% of the time among the sequences in the acceptable subset [24]. Too much deviation from this has a potential to inflate the Type 1 error rate. The subset of generated sequences with the lowest 25% of the balance metric values was considered a good tradeoff between reasonable covariate balance and validity. Our validity check within *cvcrand* showed that in this subset, the median proportion of times any two clinics were assigned the same study arm was 49% (min 27%, max 52%), which we considered acceptable. This subset of allocation sequences was presented at a public ceremony with representatives from participating clinics and other stakeholders. The ceremony was held within days of staff training and study initiation. Volunteers among attendees participated in drawing the final allocation sequence, and then participating clinics were informed of their study arm allocations. After clinic randomization, but before study initiation, it was found that one of the clinics in the control arm in South Africa did not directly provide TPT initiation services to children. A replacement with another facility with similar baseline characteristics and in the same geographical area was made.

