
In Ethiopia, data on 2020 TB notifications per clinic and region (Central, East, and South) were available to balance study arm allocations. The COVID pandemic did not significantly affect TB notifications in Ethiopia and TB notification data were therefore not averaged over time [2, 27]. We followed the same default *cvcrand* options as for South Africa. The randomization resulted in equal numbers of each region represented in each arm, and similar mean numbers of TB notifications (31 vs 33). In the subset of generated randomization sequences having the lowest 25% balance metric values, the median proportion of times any two clinics were assigned the same study arm was 43% (min 31%, max 60%). We considered this satisfactory validity, and the final sequence was randomly selected among these, and this selection was made by default within *cvcrand.* This sequence was sent to the coordinating center and site data managers. The study staff and other stakeholders in participating clinics were informed of the arm allocations in time to finalize trainings and initiate the study.

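### The primary unpaired t-test ignores the variables that constrained the allocation: it stays valid but is conservative, and a small prespecified adjustment would recover precision

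*Protocol article*

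**What the plan says.** Under Cluster selection and randomization, the Protocol article describes "constrained randomization balancing on baseline characteristics of the clinics that we believed would be associated with the primary outcome". In South Africa the variables were urban/rural, sub-district and mean 2019–2020 TB diagnoses, with the four largest clinics in a size stratum of their own. In Ethiopia "data on 2020 TB notifications per clinic and region (Central, East, and South) were available to balance study arm allocations". On the restriction it says: "The subset of generated sequences with the lowest 25% of the balance metric values was considered a good tradeoff". Ethiopia used the same 25% cut.

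Under Primary and secondary outcome analyses, the primary analysis "will be stratified by country", and "Cluster-level ratios will be compared between arms using an unpaired t-test"; the reason given is that this test holds up well when clusters are few. Two refinements follow. One is a log-transformation if the ratios are highly skewed. The other reads: "If the number of index patients varies substantially between clinics, weighted (by clinic size) mean ratios will be used". The balancing variables are not mentioned.

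The first of these sections also reports that a South African control clinic proved unsuitable after randomization but before study initiation: "A replacement with another facility with similar baseline characteristics and in the same geographical area was made".

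**The concern.** Design and analysis do not match. Restricting the draw to well-balanced sequences removes most of the balancing variables' contribution to chance differences between arms. The two-sample t-test estimates its standard error from the full spread of clinics within arms, and that spread still contains this contribution. If the variables predict the outcome, as the protocol expects, the standard error is too large for the design actually used. With nine clinics per arm in each country, clinic-level covariates are a cheap source of precision, and the listed test does not use them.

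**Working it through.** **Inputs from the Protocol article (Sample size considerations).** 18 clinics per country, 9 per arm; 80% power; 5% level (two-sided assumed); CV k = 0.35; 40 (South Africa) and 26 (Ethiopia) index patients per clinic after losses; rates 0.5 to 1 and 0.6 to 1.2, a ratio of 2. **Assumed:** R², the share of between-clinic variance explained by the balancing variables. The document gives none, so it is varied from 0 to 0.6.

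**1. The plan's own size.** The usual cluster-rate formula is c = 1 + (z₁ + z₂)² × [(λ₀ + λ₁)/y + k²(λ₀² + λ₁²)] / (λ₀ − λ₁)², with (1.960 + 0.842)² = 7.849.
- South Africa: 1 + 7.849 × (0.0375 + 0.1531)/0.25 = 6.98 per arm.
- Ethiopia: 1 + 7.849 × (0.0692 + 0.2205)/0.36 = 7.32 per arm.

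A noncentral t calculation gives 8 per arm in each. The stated 9 per arm is therefore not reproduced at 80% power. On the plan's inputs it has about 88–90% power, so there is some reserve at a ratio of 2.

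**2. Expected excess width by hand (Ethiopia, log scale).** Between-clinic variance is ln(1 + 0.35²) = 0.116. Count noise is about 1/(26 × 0.6) = 0.064 in control and 1/(26 × 1.2) = 0.032 under the intervention, a mean of 0.048. The between-clinic share is 0.116/0.164 = 0.706. Ignoring the covariates widens the interval by a factor of about 1/√(1 − 0.706 R²). The degrees of freedom and variance spent on adjustment offset this by 0.899/0.859 = 1.047, the simulated width ratio at R² = 0.
- R² 0.2: 1.079/1.047 = 1.03.
- R² 0.4: 1.180/1.047 = 1.13.
- R² 0.6: 1.318/1.047 = 1.26.

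**3. Simulation.** 4,000 runs per cell; 18 clinics; three regions plus notifications; allocation drawn from the best 25% of all 9:9 splits; Poisson counts; log cluster ratios. The unpaired t-test is compared with a linear model adding region and notifications. Each pair is unadjusted / adjusted.

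| R² | Type I error, % | Mean 95% CI width at ratio 2 (log scale) | Power at ratio 2, % | Power at ratio 1.6, % |
|---|---|---|---|---|
| 0 | 4.6 / 4.8 | 0.859 / 0.899 | 91.3 / 88.4 | 59.8 / 55.8 |
| 0.2 | 3.7 / 4.7 | 0.872 / 0.846 | 91.4 / 91.8 | 59.6 / 62.1 |
| 0.4 | 2.8 / 4.8 | 0.868 / 0.771 | 92.8 / 95.6 | 59.8 / 70.7 |
| 0.6 | 2.0 / 4.5 | 0.875 / 0.699 | 94.1 / 97.8 | 58.2 / 77.6 |

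For R² 0.2, 0.4 and 0.6 the unadjusted interval is 3%, 13% and 25% wider, in line with step 2. Under simple randomization at R² = 0.4 the t-test rejects 5.6% of true nulls, so the conservatism comes from the constraint. Further runs gave type I error of about 4%, 2.5% and 1.5–2%, and excess widths of 3–5%, 12–17% and 23–31%. They put the power loss at about 1–4 points (ratio 2) and 3–20 points (ratio 1.6).

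**4. Why the adjustment set must be small in South Africa.** With 40 index patients per clinic, ratio 2 and adjustment for every balancing variable, power at R² 0 / 0.2 / 0.4 is as follows. The number of sub-districts is assumed.
- Two sub-districts: 93/95/96% unadjusted, 88/93/97% adjusted.
- Four sub-districts: 94/94/94% unadjusted, 83/89/93% adjusted.

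**5. Replacement clinic.** If its true ratio differs by one CV (35%, assumed) from that of the clinic it replaced, the mean of nine control clinics moves by 0.35/9 = 3.9%. A true ratio of 2.0 becomes 2.0/1.039 = 1.93 or 2.0/0.961 = 2.08. This shifts the estimate and does not widen the interval.

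**The case against.** The strongest defence is that nothing here is invalid. The t-test never exceeds its nominal level in the constrained runs, a conservative test is safe in a superiority trial, and the protocol gives a reason for choosing it. At the planned doubling the reserve in the sample size absorbs most of the loss. R² is unknown, and the outcome is already a rate per index patient, so notifications may predict it only weakly. All of this stands, and it limits the point to efficiency. It does not remove it: robustness with few clusters concerns validity, and the protocol itself expects the variables to be prognostic. Nor is the reserve assured. The Limitations section expects that better care in control clinics may shrink the effect, and the South African calculation uses children under 15 although the endpoint there is under 5.

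Three stronger readings are tempting, and the document does not support them.
- A reader might infer that the t-test inflates false positives. The error runs the other way.
- A reader might infer that the benefit of balancing is lost entirely. Unadjusted power at ratio 2 still rises slightly, from 91% to 94%, as R² grows.
- A reader might infer that the substituted clinic was hand-picked, is being treated as randomized, and adds to the imprecision. The text discloses a swap for a similar facility nearby before the study began. It does not say how the facility was selected or how it will be analysed. A swap can bias the estimate but does not by that route widen intervals or cost power. A leave-out analysis is ordinary content for an analysis plan that is not shown, so its absence here is no fault.

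**Conclusion.** The point holds as one of efficiency. The stated primary test is valid but conservative for the design used. With assumed R² of 0.2 to 0.6, type I error runs from about 4% down to 1.5–2%, and intervals are about 3–30% wider than adjusted ones. The power lost is about 1–4 points at a ratio of 2 and about 3–20 points at 1.6. If R² is near zero the ranking reverses, and adjustment costs about 2–4 points. The size of the gain therefore rests on R², and the case for acting rests on the protocol's own belief that the variables matter. The main simulation has Ethiopia's covariate structure; in South Africa the gain depends on keeping the model small. It is a change worth making, not a flaw that undermines the trial.

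**What to change.** In each country, make the primary analysis a cluster-level linear regression of the ratio (log ratio if that scale is chosen) on arm plus a small prespecified set of balancing variables, with t on the residual degrees of freedom.
- Ethiopia: region and 2020 notifications (residual df 18 − 5 = 13 instead of 16).
- South Africa: urban/rural and the size stratum (residual df 18 − 4 = 14). State that sub-district is left out to save degrees of freedom.

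Keep the unadjusted t-test as a sensitivity analysis. A permutation test over the constrained sequences is an optional check where the set was saved or can be regenerated. In South Africa, state that the replacement clinic takes the slot of the clinic it replaced.

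Separately, as a minor check on bias, repeat the South African result without the substituted control clinic (9 against 8).

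The cost is wording only, since the covariates were collected for the randomization. The statistical price is 2–3 degrees of freedom and about 2–4 points of power if the covariates prove unrelated to the outcome.

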The World Health Organization (WHO) currently recommends household contact investigation for people newly diagnosed with TB in low- and middle-income countries, with an emphasis on pediatric contacts [14]. Although the aim of this policy has been to find previously undetected TB patients and reduce transmission, such investigations represent a missed opportunity to also start contacts without TB on TPT. WHO guidelines do not address the optimal implementation of TB contact investigation [14, 15]. The standard of care in most settings, or passive referral of pediatric contacts to the clinic by the index TB patient, has largely remained unsuccessful in practice. Implementation strategies to inform optimal implementation of contact management, which comprises contact investigation and TPT initiation and follow-up, among household child contacts less than 15 years are needed.

Community-based care delivery models for combined TB and HIV prevention may improve access to care for both services. Home-based contact tracing identifies more children under 5 years of age [6, 16]. The simplification of the pediatric screening process to a symptom-based approach allows for the possibility of home-based contact investigation and TPT initiation for asymptomatic children with referral of all symptomatic children. Integrated community-based pediatric TB and HIV prevention services, using existing community-based health teams in Ethiopia and South Africa, could improve access and reduce delays in the diagnosis, treatment, and prevention of TB and HIV in children. Furthermore, integrating these services into existing community-based services could make this approach cost-effective.

Few studies have evaluated the effect of home-based contact management on TPT uptake and completion in household child contacts [17, 18]. In this study, we aim to evaluate the effectiveness and cost-effectiveness of home-based contact management in two TB high-burden African countries.

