### Objectives and endpoints

The primary objective of this study is to determine the effectiveness of home-based contact management, including TPT initiation and follow-up, using community-based healthcare workers to increase TPT initiation as compared to facility-based contact management. The primary endpoint is the cluster-level ratio of the number of household child contacts less than 15 years of age in Ethiopia and less than 5 years of age in South Africa initiated on TPT (3HP, 3RH, or 6H) per index patient, comparing the intervention to the control arm (Table 1). Because we anticipate heterogeneity in the epidemiology of TB and potential differences in the response to the intervention between countries, the primary outcome will be assessed across countries and within countries.

**Table 1 Tab1:** Primary and secondary outcomes for the CHIP-TB trial

**Primary outcome**	**Outcome description**	
TPT initiation among child contacts	The cluster-level ratio of the number of household child contacts less than 15 years of age in Ethiopia and less than 5 years of age in South Africa initiated on TPT per index patient, comparing the intervention to the control arm	
**Secondary outcome**	**Outcome description**	
Child contact identification	The cluster-level ratio of the number of household child contacts less than 15 years of age in Ethiopia and less than 5 years of age in South Africa identified per index patient	
Continuum of care	The cluster-level proportions of estimated child contacts who progress through each stage of the pediatric TB prevention continuum of care (identification, screening, initiation, and completion) overall and by age, by TPT regimen, and by country. *estimated child contacts will be calculated using DHS data	
Treatment completion (as defined by WHO TPT Handbook)	• Proportion of children initiated on TPT who successfully completed TPT • Proportion of children initiated on TPT who were lost to follow-up • Proportion of children initiated on TPT with incident TB (treatment failure) • Proportion of children initiated on TPT who died • Proportion of children initiated on TPT who discontinued TPT due to: toxicity, drug-drug interaction, severe illness (e.g., malaria), pregnancy, or family preference *Treatment completion was defined as 11 doses in 16 weeks for 3HP and 68 doses in 4 months for 3RH [19].	
**Implementation outcome**	**Quantitative assessment**	**Qualitative assessment**

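### The continuum-of-care proportions have two unreconciled denominators, and the one tested between arms (identified contacts) is itself changed by the intervention

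*Protocol article*

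**What the plan says.** Table 1, under Objectives and endpoints, defines the continuum-of-care outcome as "The cluster-level proportions of estimated child contacts who progress through each stage of the pediatric TB prevention continuum of care". It lists the stages as "identification, screening, initiation, and completion" and notes that "estimated child contacts will be calculated using DHS data".

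The section Primary and secondary outcome analyses describes the outcomes differently. It says "Secondary outcomes to be compared between arms will be the number of child contacts identified" per index patient, "and the proportions of these who are screened, initiated on TPT and who complete TPT". The same paragraph sets the test: "cluster-level proportions (after a log-transformation, if necessary) will be compared using a" *t*-test. The DHS-based estimate does not appear there.

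Two neighbouring definitions matter for the repair. Contacts identified per index patient is a secondary outcome of its own in Table 1. Table 1 also has a separate treatment-completion row whose denominator is children who started TPT, and the statistical analysis section allows formal tests of other reported outcomes where there are enough events.

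**The concern.** The two definitions cannot be the same measure. In Table 1 identification is a stage with its own proportion. With identified contacts as the denominator, that stage would be 100% in both arms by construction.

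The choice matters because the two denominators respond differently to the intervention. An estimate from survey data does not depend on the arm. The number of contacts identified does: the Background states that "Home-based contact tracing identifies more children under 5 years of age", and raising identification is part of the purpose of home visits. The way identification is recorded can differ too. The community-level file is one named source for the identified count, and under Data management the Ethiopian health-post record is kept in intervention clinics only.

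A between-arm test of proportions among identified contacts therefore conditions on a post-randomisation event and compares groups that randomisation did not make alike. The Study design section also says that the data analysts are not masked. Two unreconciled denominators leave open which comparison is reported once the results are visible.

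**Working it through.** **Inputs from the article** (Sample size considerations): 30% of child contacts start TPT under standard of care; the intervention is hypothesised to double initiations per index patient; there are 1.8 (South Africa) and 2.1 (Ethiopia) children under 15 per index household.

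**The plan's own figures.** 1.8 × 0.3 = 0.54, stated as 0.5; 2.1 × 0.3 = 0.63, stated as 0.6. Both agree after rounding. The number of children per household cancels in what follows, so only the 30% and the doubling are used.

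**Assumed inputs.** Let f0 and f1 be the shares of estimated contacts who are identified in control and intervention. The article gives neither, so a range is shown.

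**Formulas.** Let R be the arm ratio of initiations per index patient.

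- Estimated denominator: control 0.30, intervention 0.30 × R, ratio = R.
- Identified denominator: control 0.30/f0, intervention 0.30 × R/f1, ratio = R × f0/f1.

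This treats estimated contacts per index patient as equal in the two arms and f0 and f1 as common to the clinics within an arm. The same form holds for screening and completion, with R replaced by the arm ratio of children screened, or completing, per index patient.

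**Results**

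| R | f0 | f1 | Initiated/estimated | Ratio | Initiated/identified | Ratio |
|---|---|---|---|---|---|---|
| 2.0 | 0.60 | 0.90 | 30% vs 60% | 2.0 | 50% vs 67% | 1.33 |
| 2.0 | 0.50 | 1.00 | 30% vs 60% | 2.0 | 60% vs 60% | 1.00 |
| 2.0 | 0.40 | 0.90 | 30% vs 60% | 2.0 | 75% vs 67% | 0.89 |
| 2.0 | 0.40 | 1.00 | 30% vs 60% | 2.0 | 75% vs 60% | 0.80 |
| 1.5 | 0.50 | 0.90 | 30% vs 45% | 1.5 | 60% vs 50% | 0.83 |
| 1.25 | 0.60 | 0.90 | 30% vs 37.5% | 1.25 | 50% vs 42% | 0.83 |

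**When the direction reverses.** R × f0/f1 < 1 requires f1/f0 > R: identification must rise by a larger factor than initiation. A child who starts TPT has been identified, so f0 is at least 0.30. Taking f1 as at most 1, reversal at R = 2 needs f0 below 0.50 and f1 more than twice f0. Smaller true effects reverse more easily, as the last two rows show. Whenever f1 exceeds f0, the ratio is below R.

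**The case against.** The strongest reply is that proportions among identified contacts are useful and do no harm beside the other outcomes. Within a clinic, initiations per index patient equal contacts identified per index patient multiplied by the proportion of identified contacts who start. A lower conditional proportion next to a higher identification count shows where children are lost; it does not contradict the primary result. This stands as a reason to keep reporting these proportions. It does not justify testing them as effects of the intervention, and it does not settle which definition of the continuum outcome governs.

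A reader might infer a firmer mechanism: that control children are mostly identified by being brought to the clinic, so nearly all of them are screened, while home visits find children who are harder to start. The article does not support this. Identification may come from the index patient's own contact report, so a child can be counted without attending. Control clinics may use community health workers to identify contacts. A standardised form is used in both arms, and the Limitations accept that control-arm contact management may improve. Nothing says that children found at home are harder to start. The arithmetic needs neither statement.

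A reader might also choose a more striking example. With Ethiopian planning values and an assumed 0.7 and 1.9 contacts identified per index patient, the proportions are 0.6/0.7 = 86% and 1.2/1.9 = 63%, a ratio of 0.74. But 0.7 is close to the floor of 0.6 initiated, so this is a near-extreme case and should not stand alone.

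Finally, the estimated denominator has a weakness: if the DHS estimate is one constant per country, the initiation-stage comparison is the primary outcome rescaled. That is true and is a cost of the repair.

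**Conclusion.** The article gives two incompatible denominators for the same secondary outcome, and the one attached to the between-arm test is a post-randomisation quantity that the intervention is designed to increase. That conflict rests on the text alone.

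Its size cannot be fixed from the article. Under the hypothesised doubling, the tested ratio would be 1.33, 1.00 or 0.89 at assumed identification of 60% vs 90%, 50% vs 100% or 40% vs 90%, against 2.0 with the Table 1 denominator. Attenuation is the consequence whenever home-based tracing identifies a larger share. Reversal is a possibility under stated conditions, and a reader should not take it as the expected outcome.

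The primary analysis is per index patient and is not affected. The point concerns the definition, testing and interpretation of secondary outcomes. It should be corrected, but it does not threaten the main conclusion of the trial.

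**What to change.** In Primary and secondary outcome analyses:

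- Use the Table 1 denominator (estimated contacts) for the between-arm comparisons of screening, initiation and completion in the continuum.
- State whether the DHS estimate is one constant per country or varies by clinic, region or age. Only with one constant per country is the arm ratio the same as for counts per index patient.
- Report the proportions of identified contacts who are screened, start and complete TPT by arm as descriptive results, labelled as conditional on identification.
- Keep the separate treatment-completion outcome among children who started TPT, labelled as conditional on initiation. Formal tests there remain possible where events allow, as the section already provides.

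The cost is wording only: the counts are already to be collected and the DHS estimate is already planned. The downside is that, with a constant estimate, the initiation-stage comparison repeats the primary analysis within each country. The text should say so, so that it is not read as independent support.
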